#### Postoperative morbidity

All postoperative morbidity will be diagnosed within 30 days after the procedure, except for postoperative diarrhea.Postoperative lymphatic leakage: Includes lymphatic fistula, lymphorrhea, lymphocele, lymphatic ascites, and special forms (chylous leakage), classified according to the Lv classification [19].Anastomotic leakage: A defect of the intestinal wall at the anastomotic site leading to a communication between intra- and extraluminal compartments. The severity is graded based on clinical management impact. Grade A anastomotic leakage results in no change in patients’ management, whereas grade B leakage requires active therapeutic intervention but is manageable without re-laparotomy. Grade C anastomotic leakage requires re-laparotomy [20].Postoperative diarrhea is loose stool, watery stool, or mucous stool three times or more a day within 6 months after the operation.

The aggregation method for all postoperative morbidities will involve calculating the proportion of patients who experience complications within the first 30 days post-operation relative to the total number of patients. Group comparisons will be conducted using the chi-square or Fisher’s exact test.

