### Sample size calculation

According to the SEER database (2004–2012) and AJCC 5th, 6th, and 7th editions, the 5-year overall survival for stage II right colon cancer was 68–84%, and for stage III, it was approximately 57 to 60% [21–23]. In the JCOG0404 trial, the 5-year overall survival for stage II-III was 91% [24]. Literature data suggests that the baseline survival for D2 lymph node dissection group is estimated to be 75% for stage II-III of the disease, and for D3 group, it is 90%, respectively. An anticipated difference of 15% in 5-year overall survival between D2 and D3 LND groups is expected. The log-rank test (Lacatos, proportion of surviving) was utilized in the PASS 11 program for sample size calculation. The power of the study is set at 80%, with a type I error 5%. An expected loss of follow-up is estimated at 15% for patients in each group. The enrollment period for patients is 3 years, and the total duration of the study will be 8 years. Based on aforementioned conditions, 239 patients should be included in the study (Table 1). Ultimately, 120 patients will be included in D3 group, and 119 patients in D2 group. The anticipated number of deaths in the D2 group is 24, and in the D3 group, it is 10.

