### Data analysis

Upon recruiting the last patient, a 5-year follow-up will commence. Intention-to-treat and per-protocol analysis will be conducted. Missing data will be imputed using Multivariate Imputation by Chained Equations (MICE package in R), except for survival data [25]. All collected data will be meticulously stored in the eCRF, and subsequent statistical analysis will be conducted. The data assessment process will be conducted in an anonymized manner, controlled by members of the university’s research group, who will solely handle the collected data. Data analysis will be solely conducted by the statisticians, also in an anonymized manner. The numeric variables will be presented as mean and standard deviation or median and range. For categorical variables, numbers and percentages will be expressed. *T*-test or Mann–Whitney *U* test will be employed for comparison between numeric variables, and chi-square or Fisher’s exact test will be used to compare categorical variables. A subgroup analysis by stage of the disease will be conducted. The survival analysis will be estimated using Kaplan–Meier curves, and comparisons will be made using the log-rank test. Cox regression will be applied to analyze the risk factors of survival. The event for overall survival will be defined as death from any cause, and for disease-free survival, it will be local or distant recurrence or death. Patients lost to the 5-year follow-up will be censored. All statistical tests are two-sided, and statistical significance is defined as *p* < 0.05. The statistical analysis will be performed in R Studio under the Affero General Public License version 3.

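### Postoperative diarrhoea is defined over 6 months, but the aggregation rule for all postoperative morbidities stops at 30 days; the two statements must be reconciled

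*Protocol article*

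**What the plan says.** The Secondary endpoint list names postoperative morbidity without a time frame. The Postoperative morbidity section under Definition of endpoints then makes three statements that bear on the window.

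- The diagnosis window, with an exception: "All postoperative morbidity will be diagnosed within 30 days after the procedure, except for postoperative diarrhea".
- The definition of the excepted item: "Postoperative diarrhea is loose stool, watery stool, or mucous stool three times or more a day within 6 months after the operation".
- The rule that produces the number to be compared between arms: "The aggregation method for all postoperative morbidities will involve calculating the proportion of patients who experience complications within the first 30 days post-operation". The denominator is the total number of patients, and the test follows: "Group comparisons will be conducted using the chi-square or Fisher’s exact test".

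The section names three morbidities: lymphatic leakage, anastomotic leakage and diarrhoea. Diarrhoea is the only one with a longer window.

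**The concern.** The first two statements set up a 6-month outcome. The third, which alone governs the analysis, covers every morbidity and stops at day 30 without repeating the exception. An analyst who follows it would leave out any patient whose diarrhoea began between day 31 and month 6, although that patient meets the trial's own definition.

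Two things are at stake. One is information on a harm that the trial singled out for longer observation. The other is freedom of choice: the trial is open-label, and while the text supports both a 30-day and a 6-month diarrhoea result, either could be chosen after the data have been seen.

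**Working it through.** **Step 1. Is the conflict settled elsewhere in the article?**

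| Place in the protocol article | What it gives | Does it settle the diarrhoea window? |
|---|---|---|
| Secondary endpoint | Name of the outcome only | No |
| Postoperative morbidity, opening sentence | 30 days, diarrhoea excepted | Points to 6 months |
| Postoperative morbidity, definition of diarrhoea | 6 months | Points to 6 months |
| Postoperative morbidity, closing paragraph | 30 days for all morbidities, no exception | Contradicts the two rows above |
| Data analysis | General tests for categorical variables, two-sided at 5% | No |
| Reporting of postoperative complication | Coding and severity grading of harms, no window | No |

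No other section gives an aggregation rule or time point for diarrhoea.

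**Step 2. How much of the defined window does the rule cover?** The plan states no figure here, so there is none to reproduce. Covered share = 30 / (days in 6 months).

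- 180 days: 30/180 = 16.7% covered, 83.3% not.
- 182.6 days: 30/182.6 = 16.4% covered, 83.6% not.
- 184 days: 30/184 = 16.3% covered, 83.7% not.

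About five sixths of the window lies outside the rule, whichever convention is used.

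**Step 3. What could that mean for the comparison?** This step is an illustration only, because the article gives neither diarrhoea rates nor onset times. Assume 6-month rates p1 and p2, let a share s of cases in both arms first appear by day 30, and take n = 119 per arm (the plan has 120 and 119). The 30-day rule then compares s·p1 with s·p2. Approximate two-sided 5% power is

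Φ{ [ |s·p2 − s·p1| − 1.96·√(2·p̄(1−p̄)/n) ] / √( [s·p1(1−s·p1) + s·p2(1−s·p2)]/n ) }, where p̄ is the mean of s·p1 and s·p2.

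| Assumed 6-month rates | s = 1 | s = 0.75 | s = 0.5 | s = 0.164 (uniform onset) |
|---|---|---|---|---|
| 10% vs 20% | 0.58 | 0.45 | 0.31 | 0.13 |
| 10% vs 25% | 0.87 | 0.73 | 0.54 | 0.21 |
| 15% vs 30% | 0.80 | 0.64 | 0.45 | 0.17 |

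If all onset is early, nothing is lost. If a moderate part is late, the loss is real. The article does not allow a choice among these columns.

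**The case against.** The strongest reply is that a sensible reader would not apply the closing sentence to diarrhoea. A specific exemption stated a few lines earlier normally overrides a general summary sentence, so this is an omission in drafting and not a decision to discard follow-up. As an account of what the authors meant, that is probably right, and it is why the point asks for reconciliation. It does not remove the conflict: the analysis sentence covers all morbidities, and it is the only rule the article gives for the comparison. Nor is this detail left to an analysis plan, since the article itself fixes both the definition and the rule.

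Two stronger readings are tempting, and the document supports neither.

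- *About 83% of diarrhoea cases are lost.* The 83% is time, not cases. A patient whose diarrhoea starts by day 30 is counted even if it lasts to month 6. Without an onset distribution, the share of cases lost could be small.
- *Early diarrhoea is pooled with leaks and hides a difference in serious events.* The aggregation sentence can mean one pooled proportion or one proportion for each complication, and the text does not say which. The section also grades anastomotic leakage and classifies lymphatic leakage, and harms are to be reported by severity grade. Nothing says that leaks will be shown only inside a pooled figure.

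**Conclusion.** The point holds as an internal contradiction in a stated analysis rule. On the literal rule, diarrhoea first arising after day 30 is left out of the arm comparison, and 30 of about 180 days (17%) of the defined window is covered. The number of cases affected cannot be derived from the article, and the power figures above rest wholly on assumed rates and onset shares. The contradiction itself needs none of those assumptions, and it holds whether the proportion is pooled or given per complication.

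The reach is narrow: one component of one secondary endpoint. Overall survival, disease-free survival, 30-day mortality and the sample size of 239 are unaffected. The text should be corrected because the repair is simple and the open choice of window is avoidable, but the main conclusions of the trial do not depend on it.

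**What to change.** Carry the exemption into the aggregation sentence. Suggested wording:

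> Postoperative morbidity is summarised in each arm as the proportion of patients with a complication by day 30, not counting postoperative diarrhoea. Postoperative diarrhoea is summarised and compared between arms as the proportion of patients meeting its definition within 6 months of surgery.

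The stated tests can stay as they are. If the authors did intend a 30-day comparison for diarrhoea, they should say so explicitly and explain how it relates to the 6-month definition.

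The change should be dated and recorded as a clarification made after recruitment ended on 11 Sep. 2023 and before arm comparisons of morbidity are run. Six months from that date is about 11 March 2024, before the article appeared on 2 July 2024. If the last patients were operated on soon after enrolment, every diarrhoea window had therefore closed by publication. The record should also state that the choice was made without sight of diarrhoea results by arm, if that is so.

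The cost is one sentence and a dated note, with no change to treatment or sample size. This assumes that stool data were collected to 6 months, as the definition implies. If they were not, the report should say so.

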#### Postoperative mortality

Postoperative mortality is defined as death from any cause within the first 30 days following the operation. It will be measured by the proportion of deceased patients relative to the total number of patients. Group comparisons will be conducted using the chi-square or Fisher’s exact test.

### Sample size calculation

According to the SEER database (2004–2012) and AJCC 5th, 6th, and 7th editions, the 5-year overall survival for stage II right colon cancer was 68–84%, and for stage III, it was approximately 57 to 60% [21–23]. In the JCOG0404 trial, the 5-year overall survival for stage II-III was 91% [24]. Literature data suggests that the baseline survival for D2 lymph node dissection group is estimated to be 75% for stage II-III of the disease, and for D3 group, it is 90%, respectively. An anticipated difference of 15% in 5-year overall survival between D2 and D3 LND groups is expected. The log-rank test (Lacatos, proportion of surviving) was utilized in the PASS 11 program for sample size calculation. The power of the study is set at 80%, with a type I error 5%. An expected loss of follow-up is estimated at 15% for patients in each group. The enrollment period for patients is 3 years, and the total duration of the study will be 8 years. Based on aforementioned conditions, 239 patients should be included in the study (Table 1). Ultimately, 120 patients will be included in D3 group, and 119 patients in D2 group. The anticipated number of deaths in the D2 group is 24, and in the D3 group, it is 10.

**Table 1 Tab1:**
[figure not shown]
Sample size calculation

### Data analysis

Upon recruiting the last patient, a 5-year follow-up will commence. Intention-to-treat and per-protocol analysis will be conducted. Missing data will be imputed using Multivariate Imputation by Chained Equations (MICE package in R), except for survival data [25]. All collected data will be meticulously stored in the eCRF, and subsequent statistical analysis will be conducted. The data assessment process will be conducted in an anonymized manner, controlled by members of the university’s research group, who will solely handle the collected data. Data analysis will be solely conducted by the statisticians, also in an anonymized manner. The numeric variables will be presented as mean and standard deviation or median and range. For categorical variables, numbers and percentages will be expressed. *T*-test or Mann–Whitney *U* test will be employed for comparison between numeric variables, and chi-square or Fisher’s exact test will be used to compare categorical variables. A subgroup analysis by stage of the disease will be conducted. The survival analysis will be estimated using Kaplan–Meier curves, and comparisons will be made using the log-rank test. Cox regression will be applied to analyze the risk factors of survival. The event for overall survival will be defined as death from any cause, and for disease-free survival, it will be local or distant recurrence or death. Patients lost to the 5-year follow-up will be censored. All statistical tests are two-sided, and statistical significance is defined as *p* < 0.05. The statistical analysis will be performed in R Studio under the Affero General Public License version 3.

### Data monitoring

An independent data monitoring committee (DMC) has been established, comprising experienced colorectal surgeons, biostatisticians, research contractors, and ethicists. A specifically assigned independent specialist will run the assessment of intraoperative field and re-evaluation process and handle the post-operative specimens according to the study design and protocol requirements. After surgery, all post-operative complications and events will be monitored by a specific physician and recorded in the eCRF. For data collection, additional specialists will be assigned who will not be involved in the perioperative management. Confidentiality agreements have been signed by all investigators involved to protect the personal information of the participants. All study-related information will be stored securely at the study site. The DMC members will convene before the commencement of the study and at regular intervals throughout its duration. The committee will assess various aspects of the study, including adverse events, participant withdrawals, and endpoints. The finial dataset will be assessed by all involved investigators and all members of DMC. The auditing will be conducted once per year and the process will be independent from investigators and the sponsor. In the event that any major changes arise during the conduct of the trial, all involved parties will convene a meeting to address potential concerns. The involved data will be stored securely for a period of 5 years after enrollment of the last participant.

### Reporting of postoperative complication

All potential harms will be collected systematically. MedDRA will be used to classify any potential harms, and all harms will be reported according to the Clavien-Dindo classification [26].

### Ethics and research registration

Comparison of D2 vs D3 lymph node dissection for right colon cancer (RICON NCT03200834) was approved by the Local Ethics Committee of Donetsk National Medical University under reference No. 24/1 dated 01/20/2017.

### Interim analysis and monitoring

An interim analysis will be conducted once, considering multiplicity using the Lan–DeMets method with O’Brien and Fleming type boundaries. The DMC will independently review the interim analysis report and prematurely terminate the study in the interest of patient safety and well-being if necessary.

## Discussion

This study is the first randomized controlled trial to evaluate the effectiveness of D3 lymph node dissection exclusively for right colon cancer based on 5-year overall survival. In the study, we intend to apply the experience in treating of right colon cancer from Japan to the East Slavic population with minor adjustments in surgical intervention. Our trial proposes the performance of only hemicolectomy, with the exception of segmental resections. The removal of infrapyloric and greater curvature lymph nodes will not be mandatory in this study. All other conditions, such as the isolation of lymph nodes on a fresh specimen, will be fulfilled.

According to the evidence-based recommendations for blinding in surgical trials [27], this study is a surgical-based RCT rather than a pharmacological one. Therefore, performance biases are impossible to exclude in this trial because patients and surgeons cannot be blinded. Patients should be clearly informed about the procedures they will undergo, as required by the healthcare systems of all centers in both countries. The primary endpoints will not be compromised by the procedures provided. All possible procedure options will be stated in the informed consent agreement without indicating the superiority of any procedure to all patients.

Additionally, the primary endpoint of this study will not be influenced by the surgeons, because a specifically assigned independent specialist will run the assessment of intraoperative field and re-evaluation process and handle the post-operative specimens according to the study design and protocol requirements. After surgery, all post-operative complications and events will be monitored by a specific physician and recorded in the eCRF. For data collection, additional specialists will be assigned who will not be involved in the perioperative management. The detection biases will not be compromised because each group of participants will be independent of each other.

The data assessment process will be conducted in an anonymized manner, controlled by members of the university’s research group, who will solely handle the collected data. Data analysis will be solely conducted by the statisticians, also in an anonymized manner.

The choice of surgical procedure, such as right hemicolectomy or segmental resection, basically depends on the proximal and distal resection margins. This decision is intricately linked to assessing the risk of paracolic lymph node involvement. Based on studies conducted on the Japanese population, 10 cm in the proximal and distal directions is considered optimal [28, 29]. In our study, we are performing hemicolectomy or extended hemicolectomy to investigate the risk of lymph node involvement in the East Slavic population, within a distance of 10 cm or more from the tumor.

There is no universally accepted consensus regarding the routine removal of infrapyloric and greater curvature lymph nodes for cancer of the hepatic flexure and transverse colon. On the one hand, these lymph nodes are derived from the dorsal mesogastrium and mesoduodenum [30, 31] and are classified as M1 according to the TNM classification for colon cancer. On the other hand, the incidence of involvement of these lymph nodes can vary from 0.7 to 11% [32, 33]. In our study, lymph node dissection of these nodes will only be performed if suspicion arises.

According to the Japanese classification of lymph nodes, the apical lymph node is located along the arterial vessels. From the 1970s to the 1990s in Japan, lymph node dissection for right colon cancer was performed along the superior mesenteric artery (SMA). However, in 1991, a cadaveric investigation conducted by Sato demonstrated that the lymphatic flow from the right colon follows the SMV instead SMA [34]. One of the first papers published in English by Toyota et al. in 1995 described the medial border of D3 lymph node dissection along the anterior surface of the SMV [29]. Currently, the medial border of D3 lymph node dissection for the right colon cancer still follows the SMV [35]. Nevertheless, the Japanese classification still demonstrates apical lymph nodes along the origin of the feeding artery, which is the SMA. Continued investigations into lymphatic flow have indicated that lymphatic vessels and lymph nodes are located not only around the SMV but also the SMA [36]. Furthermore, recent data from Japan demonstrate involvement of lymph nodes around the SMA, especially for T4 tumors [37]. In our study, the anterior surface of the SMV was selected as the surgical trunk due to new information about lymphatic outflow and the incidence of SMA lymph node involvement that emerged after the trial had begun.

The posterior location of the ileocolic artery (behind the SMV) is more common in the Russian population compared to the Chinese [38]. Lymph node dissection of apical lymph nodes remains a controversial issue, especially in patients with an ileocolic artery course behind the SMV. Thus, Spasojevic suggests removing tissue under the SMV when the ileocolic artery is located posteriorly. However, Numata demonstrates the intersection of the ileocolic artery with its posterior location relative to the SMV at its lateral edge [39]. In the RICON study, ligation of the ileocolic artery was performed at the lateral edge of the SMV, as performed by most surgeons in Japan.

One of the main challenges in lymph node dissection studies is the heterogeneity in terminology. When discussing the medial border of lymph node dissection for the right colon cancer, the concepts of D3 and CME include the removal of adipose tissue above the anterior surface of the SMV [7, 29]. The medial border during D2 lymph node dissection and non-CME shows no similarities in anatomical landmarks. The term non-CME should be avoided because any resection, such as D0, D1, D2, or any other, that differs from CME can be titled as non-CME. This can be misleading when interpreting treatment results. There is no precise definition of the medial border of D2 lymph node dissection in the literature. In some studies, the medial border of D2 lymph node dissection is considered to be the lateral edge of the SMV [16, 40, 41], while others describe D2 lymph node dissection as a conventional right colectomy [42]. In our study, the medial border of D2 lymph node dissection was closer to the terminology used by Balciscueta. This decision was also influenced by the absence of randomized trials comparing D2 or conventional lymph node dissection with D3 lymph node dissection. In our view, the evidence for the effectiveness of D3 lymph node dissection should stem from significant differences in the extent of lymph node dissection. This is one of the explanations for the 15% difference we chose for sample size calculation. In our trial, the surgical approaches differed highly than that in the RELARC trial. Thus, the effect size between these trials is different. The RELARC trial focused on the small effect size because the difference in surgical approach was superior mesenteric vein dissection [15]. Consequently, according to the effect sizes in biomedical trials reported by Christopher et al. [43], the RELARC trial aims to identify a small effect size, while the RICON trial aims to identify a medium effect size. It is encouraging that studies examining lymph node dissection techniques with less obvious differences in overall and disease-free survival are running parallel to our study [16, 40]. This collective body of research will contribute valuable insights into the effectiveness of different lymph node dissection options in the future.

